### Randomization and Blinding

Using a computerized randomization table, a statistician randomizes the patients, stratified for hospital, to 1 of the 2 communication styles (1 or 2) conducted during 3 treatment types (Type A, B, or C; Figure 1) without applying any block randomization. After the intervention therapist initially conducts the physiological measures described below, he/she receives the randomization result from the randomization table and begins the study procedure in line with the randomization result (Figure 2), according to a standardized treatment protocol. The patients and all medical and healthcare personnel, other than the intervention therapist delivering the standardized treatment protocol procedures, are blinded to the acupuncture and communication allocation (see description of treatment types below). The evaluator is blinded to allocation until after analysis of the primary outcome. This is possible because all patients and allocation groups are coded; the evaluator does not know which code means which allocation group until thereafter.

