### Study Procedure

The intervention therapist conducts the treatment procedure twice within the studied chemotherapy session. The first time (T1), illustrated with 1/2 + A/B/C in Figure 2, is conducted for 20 minutes (irrespective of verum or sham acupuncture is given) immediately pre intravenous chemotherapy. The second time (T2), also illustrated with 1/2 + A/B/C in Figure 2, is conducted for 20 minutes (irrespective of verum or sham acupuncture is given) immediately post intravenous chemotherapy. Twenty to 30 minutes is a common duration for a single acupuncture session in clinical practice.^
23
^ If the patient’s chemotherapy session lasts for 2 consecutive days, the intervention takes place on day 1. The whole study procedure lasts from the day before intervention day until day 10 after the very last chemotherapy session. Figure 2 presents the study procedure timeline.

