### The Communication Model Involving 2 Communication Styles

To manipulate the non-specific component treatment expectations during treatments,^
57
^ the intervention therapist applies a previously validated communication model,^
51
^ inspired by Kaptchuk et al,^
47
^ covering 2 verbal communication styles, where the non-verbal communication (facial expressions and body language)^48,49^ is in line with the verbal communication.

The neutral communication style: During treatment Type B-C at T1 and T2, the intervention therapist communicates at least 3 out of several neutral statements such as: “Many acupuncture studies have shown different results regarding whether or not acupuncture treatment prevents and relieves nausea,” “We don’t really know if acupuncture is a good method for producing antiemetic effects; thus we need to perform this study,” “We cannot know whether you will experience antiemetic effects of the acupuncture treatment; I have treated persons who felt differently about it.” During treatment Type A, the neutral communication is to be as similar to standard care as possible. The intervention therapist just quickly comes around, explains the data collection procedure, but does not talk explicitly about expected antiemetic effects.The positive communication style: The intervention therapist communicates at least 3 of several positive statements during treatment Type B-C such as: “Many acupuncture studies have shown that acupuncture is effective compared to medication alone,” “Patients receiving acupuncture often feel that the treatment prevents and relieves nausea,” and “I have had positive effects preventing nausea using this treatment before.” During treatment Type A, the intervention therapist communicates things such as: “Many studies show that antiemetics are highly effective in preventing and relieving nausea,” “Many patients who receive the antiemetic medication you are receiving feel that the medication prevents and relieves nausea,” and “I have met many patients who have had good effects from their antiemetics.”

The positive or neutral communication is to permeate the entire intervention. The intervention therapists are instructed to find a personal, natural way to deliver the content of the statements described above, rather than repeating them verbatim.

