The analyzer at the laboratory of each hospital at the study sites analyzes the samples using an enzyme immunoassay kit (Salimetrics LLC, USA). Regarding the precision of the measurements, the total coefficient of variation is 13.3% at 3.4 nmol/L and 6.3% at 29.4 nmol/L. The detection limit is 0.3 nmol/L. If the analyses cannot be done consecutively, the laboratory may store the samples at −20°C for up to 9 months.^
71
^ In the event of storage, the samples will be thawed at room temperature and centrifuged at 1500*g* before assay.

Treatment adherence, complications, and blinding data: At every treatment session, the intervention therapists register their adherence to the study protocol (eg, treated acupuncture points, number of needle stimulations, delivered verbal phrases). The intervention therapists register potential negative side-effects or complications occurring during the treatment sessions.

At the 10-day follow-up measure, patients respond in a binary fashion to a blinding measure^
59
^: “Do you think you have been treated with needles that have penetrated your skin, or do you think the needles have only been placed against the surface of your skin?” They also grade how certain they feel on the accuracy of their response: “Not sure at all, just guessed,” “fairly sure,” “entirely sure.” If patients have received standard care only, they choose the additional alternative “Not applicable, I did not receive any acupuncture treatment.” They respond to the question^
51
^: “During your chemotherapy session, you met an intervention therapist. Do you think you have received treatment from a therapist who emphasized the expected positive effects or one who did not?” This is measured using a 100 mm VAS anchored with 0, “Communicated very negative” and 100, “Communicated completely positive.” Patients in treatment type B-C grade their self-perceived needle-induced pain (“No/little/moderate/very painful”) and register potential side-effects of the acupuncture treatment.

Co-occurring symptoms, consumption of co-interventions: Patients repeatedly grade experience of co-occurring symptoms/problems, fatigue,^
72
^ sleeping quality,^
73
^ anxious and depressed mood,^
74
^ relaxation,^
51
^ pain and unpleasant symptoms (ie, neuropathy symptoms),^
75
^ wellbeing,^
37
^ eating capacity,^
76
^ and stool frequency.^
57

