^ This study will therefore contribute valuable evidence on 2 fronts: the potential benefit of therapists’ communication styles and the efficacy of adding antiemetic acupuncture to standard care in reducing nausea and vomiting, enhancing QoL, and improving patients’ capacity for daily and physical activities. It will also provide insights into the possible psychological and biological mechanisms through which acupuncture affects nausea and vomiting. Implementation of the results in clinical practice will be facilitated by the close collaboration between researchers and clinicians as well as the fact that the study is being conducted in a clinical oncology setting, possibly creating a pathway between research findings and clinical practice.

To conclude, this trial will contribute to the understanding of how communication can strengthen treatment expectations and thereby alleviate chemotherapy-induced nausea and vomiting. If proven effective, the communication model aimed at enhancing positive treatment expectations in patients at risk of nausea and vomiting could be implemented in routine clinical care as part of side-effect management for patients with cancer.

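### Treatment side-effects are self-reported only in the two acupuncture types, so they cannot be compared like for like with standard care, or between communication styles within standard care

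*Protocol article*

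**What the plan says.** The Data Collection section of the protocol article, in its paragraphs on treatment adherence, complications and blinding, describes two routes for recording side-effects.

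- **Patients, at the 10-day follow-up.** "Patients in treatment type B-C grade their self-perceived needle-induced pain" "and register potential side-effects of the acupuncture treatment". The item is limited to types B and C and framed around acupuncture. In the same questionnaire, standard-care patients answer the blinding question through a not-applicable option.
- **Therapists, at the sessions.** "The intervention therapists register potential negative side-effects or complications occurring during the treatment sessions". Under Randomization and Blinding, patients and all personnel "other than the intervention therapist delivering the standardized treatment protocol procedures, are blinded to the acupuncture and communication allocation". The person keeping this record is therefore the one who is not blinded.

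On the length of the sessions, Study Procedure says of the first treatment that it "is conducted for 20 minutes (irrespective of verum or sham acupuncture is given) immediately pre intravenous chemotherapy", and says the same of the second treatment after chemotherapy. For type A with neutral communication, the section on the communication model says: "The intervention therapist just quickly comes around, explains the data collection procedure, but does not talk explicitly about expected antiemetic effects". The Abstract gives two 20-minute periods for the antiemetic treatments in general.

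The Data Collection section also has patients repeatedly grade co-occurring symptoms (fatigue, sleep, mood, pain, neuropathy symptoms, eating, stool frequency and others) and quality of life. No restriction by arm is stated for these.

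**The concern.** The rule for finding side-effects depends on the arm. A bruise, sore arm or dizzy spell that appears after the session can enter the data for a type B or C patient who attributes it to the acupuncture. For a type A patient no side-effect item is described through which it could enter. Every patient is receiving intravenous chemotherapy, so such complaints have a background rate that only type A could show. Within type A, no side-effect item exists for either communication style.

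The Discussion says the trial will give evidence on "the efficacy of adding antiemetic acupuncture to standard care" and foresees routine use of the communication model if it proves effective. Benefit will be measured against standard care with the same daily form in every group. Side-effects will not be measured on the same footing, so a reader weighing the two could take the raw rate in types B and C for an added rate, or an absence of reports in type A for an absence of events.

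**Working it through.** The document gives no side-effect rate or harms calculation, so there is no figure of its own to reproduce. The check sets the sources side by side and then sizes the gap.

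**What each comparison has**

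| Comparison | Patient side-effect item | Therapist record | Symptom and quality-of-life scales |
|---|---|---|---|
| Verum vs sham | Same item, patients blinded, 20 minutes each | Unblinded, equal session time | Both |
| Positive vs neutral within B and C | Same item | Unblinded | Both |
| B and C vs A | B and C only | Unblinded; shorter visit explicit for A with neutral communication | Both |
| Positive vs neutral within A | None | Unblinded; quick visit in the neutral group | Both |

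The first two rows are like for like on the patient item. The last two are not.

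**Group sizes.** Inputs: 198 patients (Sample Size) and approximately equal allocation to six groups (Figure 1 caption).
- Type A: 198/3 = 66.
- Types B and C: 198 × 2/3 = 132.
- Type A with neutral communication: 198/6 = 33.

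**Precision if type A were asked.** Assumed rates, not in the document: 20% in B and C, 15% in A.
- SE = √(0.20 × 0.80/132 + 0.15 × 0.85/66) = √(0.00121 + 0.00193) = 0.056.
- Half-width = 1.96 × 0.056 = 0.11. The 5-point excess would carry a 95% interval of about −6 to +16 points.
- Range, with equal rates in all groups and 1/66 + 1/132 = 0.0227: at 10%, 1.96 × √(0.10 × 0.90 × 0.0227) = 0.09; at 30%, 1.96 × √(0.30 × 0.70 × 0.0227) = 0.14.

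As now planned, only the 20% would be observed by self-report.

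**What unequal capture could do if counts were compared anyway.** All rates are assumed, and the true rate is 20% in every group.
- Capture of 90% in B and C and 30% in A gives observed rates of 0.20 × 0.90 = 18% and 0.20 × 0.30 = 6%.
- Pooled rate = (66 × 0.06 + 132 × 0.18)/198 = 0.14. SE under no difference = √(0.14 × 0.86 × 0.0227) = 0.0523. SE at the observed rates = √(0.06 × 0.94/66 + 0.18 × 0.82/132) = 0.0444.
- Chance of a two-sided P < .05 = Φ((0.12 − 1.96 × 0.0523)/0.0444) = Φ(0.39), about 65%.
- With 50% capture in A (18% vs 10%), the same formula gives about 30%.

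**The case against.** The strongest reply is that no stated aim fails. The objectives are nausea, vomiting, quality of life and activity. The Discussion describes the standard-care group as a comparator for additional nausea reduction, and its sentence on adding acupuncture speaks of efficacy. This stands: a harms comparison with standard care is not promised, so the point is a weakness in a stated collection rule and not a contradiction.

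A second reply is that this is a condensed article, the item is paraphrased, the assessment schedule in Figure 3 is not shown, and a fuller safety section may exist. That limits what can be said about the exact wording. It does not remove the point, because the article itself states who is asked and about what.

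A third reply is that much remains comparable, and this also stands. A reader might infer that no harm of any kind can be compared with standard care. The document does not support that: pain, fatigue, mood, sleep, eating and quality of life are self-graded with no arm restriction, and heart rate and blood pressure are measured twice. These allow a partial comparison, though none is described as recording unwanted effects attributed to the treatment or visit. A reader might also infer that sessions are shorter throughout type A. A quick visit is explicit only for type A with neutral communication, about 33 patients. The Abstract implies two 20-minute periods in general, and the physiological-data paragraph describes about 10 to 15 minutes of introductory contact before treatment in any type.

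Finally, the ±11 points show that the added item would not separate a small excess from background. That is correct and limits what the fix can deliver.

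**Conclusion.** The point holds for treatment side-effects. Self-report is confined to types B and C and to effects of acupuncture, and the only other side-effect record is unblinded and in-session. Acupuncture against standard care, and communication style within type A, therefore have no like-for-like side-effect comparison. About 66 of 198 patients have no self-report item, assuming near-equal allocation.

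Verum versus sham and communication style within B and C are sound on the patient item, and the general symptom scales are usable across all groups. Verum versus sham does not, however, show what adding a needling procedure does: both groups receive one, and they differ in penetration, point and needle sensation.

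The primary outcome is not affected. The change is worth making because it is cheap and the document looks ahead to clinical use. The ±11 points, and the 30% to 65% chance of a spurious difference, rest wholly on assumed rates and serve as illustration.

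**What to change.** 1. On the existing 10-day questionnaire, ask all six groups one neutrally worded question on any unwanted effects since the study session, with a description and the day. Keep needle pain and acupuncture-specific effects as type B and C items.
2. Report therapist-recorded events separately, labelled as unblinded and confined to the sessions.
3. Reconcile the Abstract, Study Procedure and the communication-model section on how long the therapist's session lasts in type A, so that observation time by group is known.
4. Present the contrast with type A as descriptive.

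The question should not go on the daily form for days 0 to 4. That is the primary-outcome window, and a daily prompt about unwanted effects could prime nausea reports in a trial that manipulates expectations. Nor should answers be forwarded to the clinics as part of this change: patients are assured that cancer care personnel will not manage their responses.

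The cost is one question on a form that every group already completes. Some unrelated chemotherapy complaints will need sorting. Recruitment is described as under way, so patients already enrolled will lack the item and the type A contrast will be less precise than the figures above. Type A patients also know that they had no needles, so that contrast is not patient-blinded.

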### Data Analysis Plan

The intention-to-treat principle will be applied when analyzing the study data, that is, all patients will be analyzed as randomized, regardless of whether they complete the study procedure as planned. The primary parameters of interests are the 2 factorial effects (2 main effect, ie, 1. communication style, and 2. treatment type, and one interaction, ie, treatment expectations) during the first 5 days of the studied chemotherapy session period. The evaluator will use a generalized linear mixed effects model (GLMM) to determine if the independent variables communication style and treatment type affect the dependent variable nausea. We take the stratified randomization into account (adjusting for random effects of department on the outcomes) and include baseline characteristics in the analysis model to increase the precision of the estimates.^
77
^ In secondary GLMMs, we will study the effects of the variety of independent variables on vomiting, QoL, and daily and physical activity. Patients who cease to participate (dropouts) and missing data will be handled according to routines as follows. In the main analysis, missing data will be handled using multiple imputations by chained equation.^
78
^ We will specify the multiple imputation model (the choice of auxiliary variables) after comparing patient characteristics between those with complete and those with incomplete data. Under the assumption that data are missing at random, an analysis based on multiple imputation conforms with the intention to treat. We will then also estimate the factorial effects using complete data only. We will conduct a sensitivity analysis by comparing estimates regarding the 2 main effects described above with estimates based on complete data only, in other words, a pattern-mixture model and tipping point analyses. Statistical significance will be defined as a 2-tailed *P* < .05, and the analyses will be performed in IBM SPSS statistics (IBM Corp, Armonk NY, USA).

In line with previous recommendations regarding cost-effectiveness analysis alongside clinical trials, we will specify the methods for cost effectiveness analysis after evaluating these outcomes. If the present evaluation shows significant health benefits on the primary outcome measure, or in at least on 1 secondary outcome, a cost-effectiveness analysis of our intervention will be conducted using a model-based approach.^
79
^

External study monitoring will be conducted according to the guideline for good clinical practice adapted to non-medical studies. Independent observations will be conducted regarding the intervention physiotherapists’ compliance to the standardized treatment protocol during 1/2 + A/B/C, and the validity results will be presented.

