**Methods::**

This is a trial protocol for a randomized, sham-controlled, patient- and evaluator-blinded clinical trial. Patients (n = 198 patients according to a sample size calculation) with breast, colorectal, or bladder cancer undergoing neo-/adjuvant moderately to highly emetogenic chemotherapy are being randomized in 2 × 3 factorial design to the following conditions: 1. neutral or 2. positive communication style regarding expected treatment effects, during the antiemetic treatment types: A) standard care only (including antiemetics, no acupuncture), or, in addition to standard care, B) sham acupuncture with telescopic non-penetrating needles, or C) verum, penetrating acupuncture. The 2 communication styles 1 and 2 are carried out during the antiemetic treatments given by an intervention therapist immediately pre and post (20 minutes × 2) an intravenous chemotherapy session. Data are being collected at baseline on the day before the chemotherapy session, daily for 10 days, at a 10-day follow-up, and at a follow-up after completing the entire chemotherapy period, lasting about 6 months. Primary outcome is mean score Visual Analog Scale nausea grading for the first 5 days of the chemotherapy session period. Secondary outcomes are for example, vomiting, treatment expectations, QoL, daily and physical activity, and physiological measures. Treatment effect modifiers will be analyzed, for example, blinding success, treatment expectations, and previous nausea experiences.

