The main study hypothesis is that positive communication plus acupuncture (penetrating verum or non-penetrating sham acupuncture) is more effective than neutral communication plus standard care for nausea, calculated as the mean score for the first 5 days of the studied chemotherapy session period. We hypothesize that treatment expectation is a mediator of the effects.

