## Methods

### Design

The study uses a randomized sham-controlled design. The design is a 2 × 3 factorial design^
53
^ where patients are randomized to the communication styles 1. neutral communication, or 2. positive communication, given when undergoing 1 of 3 antiemetic treatments (Figure 1). All patients receive standard care; patients randomized to antiemetic treatment type B (sham acupuncture), or C (verum acupuncture) receive the acupuncture therapy in addition to A (standard care). The structure of the intervention follows the Template for Intervention Description and Replication (TIDieR) checklist^
54
^ and the Standard Protocol Items: Recommendations for Interventional Trials (SPIRIT).^
55
^

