Self-reported descriptive data: On a baseline questionnaire, patients supply sociodemographic data (eg, sex, age, level of education, profession), clinical data (eg, comorbidities, disease-specific variables, medications), data on previous experience of and belief in acupuncture effects,^
22
^ data on previous nausea experiences in their lives and specifically when undergoing cancer therapy, self-predicted risk for nausea,^
36
^ and data regarding therapeutic alliance, for example, to which extent the patient trusts the therapist to be able to help him/her.^
61
^

Data on nausea and vomiting: Patients complete a measure of nausea and vomiting^
7
^ daily for 10 days, answering questions about the primary outcome (nausea intensity) and the secondary outcomes (nausea occurrence, duration of nausea, vomiting episodes, and consumption of antiemetics). This measure asks the following questions with reference to the past 24 hours: “Have you experienced nausea?” (“No” / “Yes”); “How intense was the nausea?” A 100 mm VAS with verbal anchors “No nausea” and “Worst possible nausea” is used. The accumulated duration (in minutes) of nausea within the past 24 hours is registered. Patients also respond to the questions: “Have you vomited?” (“No”/“Yes”), “How many episodes?” (number of episodes is given), and “Have you consumed rescue antiemetics?” (“No”/“Yes”). They are asked to: “Please detail agent, dose and frequency of each antiemetic agent used.” Also, other kinds of nausea and vomiting-related care consumption is self-registered. Burden is asked for and registered on 2 separate 100-mm VAS: “Did the nausea negatively affect your daily life?.” The same question is posed regarding vomiting, both anchored with 0 (“Not affected at all”) and “100” (“Affected in the worst possible way”; Figure 2).

Expectations data: Patients rate their treatment expectations daily for 10 days, using a valid expectancy measure,^
56
^ “Do you believe that the treatment you are going to receive is effective for nausea and vomiting?” This is measured using a 100 mm VAS anchored with 0 (“I don’t believe at all that it’s effective”) and 100 (“I completely believe that it’s effective”). Post-treatment, the question is written with the modified verb tenses “received” and “was.”

Treatment satisfaction data: On day 10 after the intervention, patients rate their interest in receiving future acupuncture treatment by answering the questions^
37

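### The primary analysis names treatment expectations, the hypothesised mediator, as its factorial interaction, where a 2 × 3 design has communication style × treatment type

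*Protocol article*

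**What the plan says.** All references are to the protocol article.

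- **Design:** "The design is a 2 × 3 factorial design", with two communication styles crossed with three treatment types.
- **Data Analysis Plan, primary parameters:** "The primary parameters of interests are the 2 factorial effects". The parenthesis that follows has three items: the main effect of communication style, the main effect of treatment type, and "one interaction, ie, treatment expectations".
- **Data Analysis Plan, next sentence:** the GLMM is to "determine if the independent variables communication style and treatment type affect the dependent variable nausea". Expectations are not among these variables.
- **Introduction, main hypothesis:** "We hypothesize that treatment expectation is a mediator of the effects".
- **The Communication Model Involving 2 Communication Styles:** the model is applied "To manipulate the non-specific component treatment expectations during treatments".
- **Data Collection, expectations data:** "Patients rate their treatment expectations daily for 10 days", with past-tense wording after treatment.
- **Abstract, Methods:** "Treatment effect modifiers will be analyzed, for example, blinding success, treatment expectations, and previous nausea experiences".
- **Sample Size:** 198 patients, 99 per communication style, to detect 10 mm on a 100 mm VAS between positive and neutral communication, two-sided alpha .05, power 80%.

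**The concern.** A two-factor design has one interaction, the product of the factors. Here that is communication style × treatment type, with (2 − 1) × (3 − 1) = 2 df. The plan puts a measured patient variable in its place. Across the article that variable has three roles: mediator, effect modifier and primary interaction.

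Two things are at stake.

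1. **The estimand.** If an expectation score rated after the communication enters the primary model, the communication coefficient becomes an effect at fixed expectation. That is not the total effect of being randomised to positive communication, which the trial was sized for and which the intention-to-treat principle calls for.
2. **The term that is not named.** The communication contrast is built differently by treatment type. With either acupuncture type, the neutral style voices uncertainty about acupuncture. With standard care, it avoids the subject of expected effects. The positive messages also differ, promoting acupuncture in one case and antiemetics in the other. The main hypothesis compares particular combinations of the two factors. Whether the communication effect varies by treatment type therefore bears on how the main effects are read.

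**Working it through.** **Step 1. The planned sample size.** Inputs from Sample Size: difference 10 mm, two-sided alpha .05, power 0.80, 99 per group. No SD is given, so I solved for it:

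SD = 10 / [(1.960 + 0.842) × √(2/99)] = 25.1 mm.

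With an assumed SD of 25 mm, n = 2 × (1.960 + 0.842)² × 25² / 10² ≈ 98.1, rounded up to 99 per group (198 in total), with power 0.80. The figure of 198 therefore matches an SD near 25 mm and refers to the communication main effect with no expectation term. At 99 per group, power would be 0.94 with SD 20 mm and 0.65 with SD 30 mm.

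**Step 2. What an expectation term would do.** Assumed, not in the protocol: within-arm SD 25 mm for nausea and for expectation; communication raises expectation by 10, 15 or 20 mm; the total effect is −10 mm; a share *p* of it is mediated. The data model was

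- expectation = 50 + shift × C + error
- nausea = 40 − 10(1 − *p*) × C − *b* × (expectation − 50) + error, with *b* = 10*p* / shift

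where C is 1 for positive communication. The error variance of nausea was set so that its within-arm SD stays at 25 mm. Each setting had 3,000 simulated trials of 198 patients, analysed by least squares on communication and two treatment-type indicators, with or without expectation (centred) and its product with communication.

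| Share mediated | Communication coefficient, expectation in model | Power |
|---|---|---|
| 0% | about −10 mm | 0.73–0.77 |
| 25% | about −7.5 mm | 0.48–0.56 |
| 50% | about −5 mm | 0.27–0.32 |
| 75% | about −2.5 mm | 0.11–0.17 |
| 100% | about 0 mm | about 0.05 |

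The ranges run over the three shifts. Full mediation with a 10 mm shift leaves no residual variance under these SDs, so the last row uses 15 and 20 mm only. Without expectation in the model, the coefficient stayed near −10 mm and power was 0.78–0.81 in every setting.

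If the score is not centred, the coefficient is the effect at expectation 0, and its power is only 0.18–0.22 even with no mediation.

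**Step 3. The interaction that belongs to the design.** With 198 / 6 = 33 per cell and assumed SD 25 mm, the difference in communication effect between two treatment types has

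SE = 25 × √(4/33) = 8.70 mm.

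For a true difference of 10 mm, power ≈ Φ(10/8.70 − 1.960) = Φ(−0.81) ≈ 0.21.

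**The case against.** The strongest reply is that no model containing expectations is actually specified. The GLMM sentence names only the two randomised factors, the other covariates mentioned are baseline characteristics, and the sensitivity analysis concerns the two main effects. The phrase may be a mislabelled communication × treatment type interaction, or a mediation aim in the wrong place; the Discussion does say that expectations will be analysed as a psychological mechanism. The text does not say which expectation rating would be used or which factor it would interact with. The item also has prospective wording, and the schedule figures are not shown, so a pre-treatment rating may exist. Such a rating could properly be an effect modifier and would not block the communication effect.

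Most of this stands, and it rules out two stronger readings:

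- A reader might infer that the primary model, fitted as written, removes the communication effect. The text does not fix such a model. Removal would also need full mediation, and the hypothesis calls expectation a mediator, not the only one. The mediated share is not given.
- A reader might infer that the true interaction will never be tested. The article only fails to name it, and an analysis plan that is not shown may do so.

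The reply does not rescue the phrase. The article positively names the wrong term among the primary parameters, and the next sentence disagrees with it.

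**Conclusion.** The concern holds as a misdefined primary interaction that conflicts with the plan's own model sentence. This follows from the text alone and needs no assumption. Two analysts could follow the same paragraph and report different communication effects.

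The loss of effect and power is conditional: it arises only if a post-randomisation expectation score enters the primary model. Its size rests on the assumed SDs, expectation shift and mediated share, so the table illustrates what could happen and does not forecast this trial. The effect is attenuated under partial mediation and disappears only under complete mediation. The sample size of 198 is not affected.

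**What to change.** In the Data Analysis Plan:

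1. Replace the phrase with: one interaction, ie, communication style × treatment type (2 df). Make the count of primary parameters and the GLMM sentence agree with it.
2. State that no variable measured after randomisation enters the primary model.
3. Analyse post-randomisation expectations in a separate mediation analysis. A pre-randomisation rating, if one is collected, may serve as a covariate or effect modifier.
4. Report the interaction as an estimate with a confidence interval, and do not take a non-significant test as proof that the communication effect is the same across treatment types.

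The cost is a few sentences and no change to data collection; it should be settled before unblinding. The downside is the low power of the interaction (about 0.21, Step 3), which the plan should disclose.
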